**Index**

[1. Background 3](#_Toc213415097)

[2. Objectives 3](#_Toc213415098)

[3. Methods 3](#_Toc213415099)

**[3.1.](#_Toc213415100)****[Study design](#_Toc213415100)** [3](#_Toc213415100)

**[3.2.](#_Toc213415101)****[Study population](#_Toc213415101)** [3](#_Toc213415101)

**[3.3.](#_Toc213415102)****[Randomization](#_Toc213415102)** [4](#_Toc213415102)

**[3.4.](#_Toc213415103)****[Interventions](#_Toc213415103)** [4](#_Toc213415103)

**[3.5.](#_Toc213415104)****[Outcomes](#_Toc213415104)** [4](#_Toc213415104)

**[3.6.](#_Toc213415105)****[Data collection and follow up](#_Toc213415105)** [5](#_Toc213415105)

**[3.7.](#_Toc213415106)****[Statistical Considerations](#_Toc213415106)** [5](#_Toc213415106)

[4. Monitoring and Oversight 6](#_Toc213415107)

[5. Ethics and Dissemination 7](#_Toc213415108)

**[5.1.](#_Toc213415109)****[Research Ethics Approval](#_Toc213415109)** [7](#_Toc213415109)

**[5.2.](#_Toc213415110)****[Informed Consent](#_Toc213415110)** [7](#_Toc213415110)

**[5.3.](#_Toc213415111)****[Protocol Amendments](#_Toc213415111)** [7](#_Toc213415111)

**[5.4.](#_Toc213415112)****[Dissemination Policy](#_Toc213415112)** [7](#_Toc213415112)

1. **Background**

China is a high-burden country for tuberculosis (TB). Mathematical models suggest that even under the most optimistic diagnosis and treatment scenario, it will be difficult to achieve the current global TB control targets in China ^[1]^. Therefore, it is necessary to strengthen the management of latent tuberculosis infection (LTBI) and TB preventive treatment (TPT) for high-risk populations.

Patients with rheumatic diseases (RDs) are high-risk groups for TB infection and disease. Rheumatic diseases affect more than 20 million people in China., accounting for 20% of the global burden. Our study (epidemiological study and therapeutic evaluation of rheumatic patients with tuberculosis, ETHERTB) has found that the prevalence of active tuberculosis (ATB) among RDs patients is 882/100,000, significantly higher than that of the general population.

The LTBI population have a 5%-10% lifetime risk of progressing to ATB^[2, 3]^. The prevalence of LTBI nearly 20% in China ^[4]^. Due to the underlying disease and use of immunosuppressive medications, the risk of developing ATB in RDs patients is much higher than that of the general population. Therefore, conducting TPT among RDs patients with LTBI in China is of great significance in reducing the incidence and mortality of TB.

Nine-month isoniazid (INH) monotherapy (9H) is a standard TPT regimen recommended by the WHO. However, its effectiveness is limited by poor treatment complicance, partly owing to the long duration of the regimen. WHO recommended a 3-month regimen of weekly rifapentine (RFT) and INH (3HP) as an alternative ^[5]^. However, the safety profile of 3HP in Chinese population raises concerns ^[6]^.

Due to the high clinical heterogeneity, complex disease conditions and medications in RDs patents, the high-quality studies on TPT in this population is very limited. Considering the high risk of ADRs due to existed organ damage and concomitant medication which is almost inevitable in RDs patients, TPT regimens should be selected with caution. Based on previous studies and clinical experience from our center, we modified the 3HP regimen to 3HP-PUMCH, which involves twice weekly RFT at 450mg and daily INH at a maximum dose of 300mg for 3 months. We evaluated the efficacy, safety and completion of 3HP-PUMCH compared to the standard 9H regimen in high-risk RDs patients with LTBI.

1. **Objectives**
   1. To determine the non-inferiority of the 3HP-PUMCH regimen compared to the standard 9H regimen in preventing ATB in high-risk RDs patients with LTBI.
   2. To compare the safety profile and treatment completion rates between the two regimens.
2. **Methods**
   1. **Study design**

The study is a multi-center, open-label, non-inferiority, randomized controlled trial.

- 1. **Study population**
     1. Eligible criteria

1. Aged 18-70 years;
2. Diagnosed with at least one of the high-risk RDs including systemic lupus erythematosus (SLE), Takayasu's arteritis (TA), Behcet's disease (BD), primary Sjogren's syndrome (SS), rheumatoid arthritis (RA) and ankylosing spondylitis (AS);
3. Not currently using biologics;
4. Taking any of the following medications: ①≥15mg daily of prednisone or equivalent; ②at least one of the following immunosuppressive agents: methotrexate (MTX), cyclophosphamide (CTX), mycophenolate mofetil (MMF), cyclosporine A (CsA), azathioprine (AZA), tacrolimus (FK-506), leflunomide, iguratimod and tripterygium wilfordii; ③initiating TNF inhibitors treatment.
5. Positive for blood T-SPOT.TB (≥24 SFCs/10^6^ PBMC).
   - 1. Exclusion criteria:
6. Suspected or confirmed ATB,
7. Seropositive status for HIV-Ab,
8. Seropositive status for HCV-Ab or HBV surface antigen,
9. Severe liver damage (total bilirubin > 3mg/dL or aminotransferase > 2ULN) or liver cirrhosis,
10. Prior use of TPT,
11. History of allergy to INH or RFT,
12. Pregnancy or lactation.
    1. **Randomization**

Participants were randomly allocated in a 1:1 ratio into the 9H and 3HP-PUMCH groups using a computer-generated random sequence. Randomization was stratified in the research center. A random sequence was generated using a fixed-block randomization method with a block length of 4. Allocation concealment was maintained using a web-based central randomization system.

- 1. **Interventions**
     1. Experimental Group

3HP-PUMCH regimen: INH once daily, 5 mg/kg (with a maximum daily dose of 300 mg), combined with RFT twice a week, 450 mg each time, for 3 months.

- - 1. Control Group

9H regimen: INH once daily, 5 mg/kg (with a maximum daily dose of 300 mg), for 9 months.

- - 1. Concomitant Treatment

RDs Treatment: The patient's baseline RDs treatment was followed according to the best available clinical guidelines/consensus and adjusted as needed by the treating clinician. A uniform RD treatment regimen was not stipulated.

- 1. **Outcomes**
     1. **Primary outcomes**

The occurrence of ATB up to the end of the follow-up period (24 months after randomization).

1. Diagnosis criteria:

- Microbiologically confirmed ATB: Biological specimens were positive by smear microscopy, culture, Xpert MTB/RIF, or other molecular biological diagnostic methods.
- Clinically diagnosed ATB: A clinical diagnosis of ATB was made when patients present characteristic symptoms (e.g., fever, cough, chest pain, night sweats, weight loss), supported by highly suggestive laboratory and imaging findings. Additionally, the diagnosis must be corroborated by a positive response to empiric TB treatment.

1. Diagnosis Adjudication:

All suspected ATB cases were reviewed by an external Endpoint Event Adjudication Committee (comprising two TB and one rheumatology experts) who were blinded to the TPT regimen allocation.

- - 1. **Secondary outcomes**

1. Permanent discontinuation of TPT due to serious adverse events (SAEs) or ATB occurrence.
2. ADRs related to prophylactic drugs (assessed by WHO-UMC causality criteria).
3. Completion rate of TPT.

Completion of treatment are defined as the consumption of at least 22 doses of RFT and at least 81 doses of INH within 16 weeks for the 3HP-PUMCH group, and 243 doses of INH within 52 weeks for the 9H group.

- 1. **Data collection and follow up**
     1. **Data collection:**

Patient data will be collected by trained researchers using a standardized case report form (CRF). At baseline, demographic characteristics, diagnosis and course of RDs, current medication use (including glucocorticoids and/or immunosuppressants), and a series of laboratory tests will be conducted to assess participants' general health. These tests will include hematological parameters, liver and renal function, inflammatory markers, and fasting blood glucose.

- - 1. **Follow-up procedures:**

Participants in the 3HP-PUMCH group will attend outpatient follow-up visits at their recruitment center at months 1, 2, and 3 during preventive treatment. At each visit, clinical assessments and laboratory tests, including hematological parameters and liver and renal function tests, will be conducted. Medication adherence and adverse events will be documented, with particular attention to any drug-related side effects. After completing TPT, participants will return for follow-up visits at months 6, 12, 18, and 24 to assess the incidence of ATB.

Participants in the 9H group will attend outpatient follow-up visits at months 1, 2, 3, 6, and 9 during preventive treatment. The same set of clinical and laboratory assessments, as well as monitoring for medication adherence and adverse events, will be performed. Post-treatment visits will also be conducted at months 6, 12, 18, and 24 to record any incidence of ATB.

- - 1. **Medication adherence assessment**

Medication adherence will be evaluated using the 8-item Morisky Medication Adherence Scale (MMAS-8). The MMAS-8 is a self-reported questionnaire that categorizes adherence as high, medium, or low based on the total score. Assessments will be conducted at each follow-up visit during preventive treatment.

- 1. **Statistical Considerations**
     1. **Sample Size Calculation**

1. Baseline Risk Assumptions: The 2-year incidence of ATB in the 9H group is approximately 3.6% (annual incidence of 1.8%). This estimate is based on cohort studies conducted in high TB burden countries/regions^[7]^, with a focus on populations at high risk for TB, such as those receiving high-dose glucocorticoids or immunosuppressive treatment, or planning to receive iTNF. The study inclusion criteria clearly define this high-risk subgroup, rather than evaluating all patients with RDs in general. While no study has specifically included RD patients with these risk factors, the incidence estimate in this study is derived from available data in high-risk populations.
2. Non-Inferiority Margin (Δ): The pre-set margin is 1.4% (absolute risk difference). This margin is determined based on the clinically acceptable increase in risk (i.e., the maximum additional risk allowed for 3HP-PUMCH relative to 9H).
3. Expected Effect and Sample Size Limitation: The expected incidence in the 3HP-PUMCH group is 1.1% (with an expected risk difference of -2.5%). This hypothesis is informed by similar studies in the HIV population, which observed 1.01% vs 3.50% cumulative TB rates, yielding a risk difference of −2.49% in favour of 3HP^[8]^. While standard non-inferiority designs typically assume a 0% risk difference, this study incorporates this assumption based on the higher adherence and better protective effects of the short-course regimen containing rifapentine in clinical practice, as well as the expected reduction in toxicity with the modified regimen. This design reflects a practical clinical approach under conditions of limited resources and a lack of sufficient evidence. We acknowledge that this assumption might result in a sample size that may not meet statistical power requirements under a 0% risk difference assumption, which is one of the limitations of this study.
4. Statistical Power: 80% statistical power, one-sided alpha level of 0.025.
5. Sample Size Calculation: 236 participants per group.
6. Total Sample Size (Accounting for Attrition): Assuming a 10% attrition rate, a total of 526 eligible participants will be enrolled.
   - 1. **Analysis Sets**
7. Primary Analysis Set (mITT): The Modified Intention-to-Treat (mITT) analysis set includes all participants who were randomized and received at least one dose of the intervention drug.
8. Sensitivity Analysis Set (PP): The Per-Protocol (PP) analysis set includes all participants from the mITT set who completed the TPT.
   - 1. Statistical Methods
9. Primary Outcome Analysis

- The cumulative incidence and its 95% CI will be estimated using the Exact Method.
- Non-inferiority will be concluded by comparing the upper bound of the 95% CI for the difference in cumulative incidence with the pre-set non-inferiority margin (1.4%).
- Non-Inferiority Test Criteria: If the upper bound of the 95% CI is < 1.4%, non-inferiority will be considered demonstrated.
- Superiority Test: If non-inferiority is achieved, a further assessment will be made to determine whether the upper bound of the 95% CI is < 0.0% to test for superiority.

1. Secondary Outcome Analysis

Descriptive statistical methods will be used. The rates of adverse drug reactions (ADR), liver toxicity, and other outcomes will be compared using chi-square tests, and 95% CIs will be calculated.

1. Sensitivity Analysis

In the mITT population, incidence rates per person-year will be calculated, and the difference in incidence rates and its 95% CI will be estimated.

1. Software

Analysis will be conducted using R software (version 4.4.1).

1. **Monitoring and Oversight**

The trial is overseen by a Coordinating Center (Peking Union Medical College Hospital). An external Endpoint Event Adjudication Committee is established to independently review and validate all primary outcome events (ATB), ensuring objectivity and consistency.

1. **Ethics and Dissemination**
   1. **Research Ethics Approval**

This study received approval from the Ethics Committees of the participating hospitals (Approval Number: JS-1498). All procedures comply with the ethical standards of the institutional and national research committees and with the Helsinki declaration.

- 1. **Informed Consent**

All participants provided written informed consent prior to enrollment in the study.

- 1. **Protocol Amendments**

Any substantial changes to the protocol will be submitted to the Ethics Committees for approval and will be updated in the trial registry (ChiCTR).

- 1. **Dissemination Policy**

The results of this study will be published in peer-reviewed journals (such as this manuscript) and presented at scientific conferences. The final protocol will be accessible to readers as supporting information accompanying the main manuscript. All authors meet the criteria for authorship.

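### Fixed blocks of 4 within centre, in an open-label trial, let an informed recruiter know up to one third of allocations in advance

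*Protocol*

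**What the plan says.** Protocol section 3.1 (Study design): "The study is a multi-center, open-label, non-inferiority, randomized controlled trial".

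Protocol section 3.3 (Randomization) gives four facts:
- Ratio and method: "Participants were randomly allocated in a 1:1 ratio into the 9H and 3HP-PUMCH groups using a computer-generated random sequence".
- Stratification: "Randomization was stratified in the research center". The wording is loose, but stratification by centre is the natural reading.
- Blocking: "A random sequence was generated using a fixed-block randomization method with a block length of 4".
- Concealment: "Allocation concealment was maintained using a web-based central randomization system".

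Section 3.5 (Outcomes) adds that suspected tuberculosis cases go to an external committee of experts "who were blinded to the TPT regimen allocation".

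The protocol does not say whether recruiting staff knew the block length or whether it was withheld from them. It does not give the number or size of the centres.

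**The concern.** Concealing the list protects enrolment only if the next entry cannot be worked out from the entries already seen. Here treatment is known once assigned, each centre runs its own sequence, and every block holds exactly two allocations to each arm. Anyone who keeps count can see when one arm is used up.

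Recruiters could have reasons to prefer an arm for a given patient. The Background voices concern about the safety of 3HP in Chinese patients and about adverse reactions where there is organ damage or concomitant medication. It also describes 9H as limited by poor compliance. Eligible patients vary widely in risk: six diseases, with steroids, a range of immunosuppressants or the start of a TNF inhibitor. Bringing an enrolment forward or holding it back could therefore make the arms differ in baseline risk. Blinded adjudication acts after enrolment and cannot correct that.

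**Working it through.** **Inputs.** From sections 3.1 and 3.3: open label, 1:1, by centre, fixed blocks of 4. From section 3.7: 2-year risk 3.6% (9H) and 1.1% (3HP-PUMCH), margin 1.4%, 80% power, one-sided alpha 0.025, 236 per group, 10% attrition, 526 in total.

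**1. The plan's own figure.** The protocol gives no figure for predictability. Its sample size reproduces:

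n = (1.96 + 0.842)² × (0.036 × 0.964 + 0.011 × 0.989) / (0.014 + 0.025)² ≈ 235.2, rounded up to 236. Then 236 / 0.9 ≈ 262.2, rounded up to 263 per arm, and 2 × 263 = 526. The block scheme does not affect this.

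**2. Allocations known with certainty.** There are six equally likely blocks: AABB, BBAA, ABAB, ABBA, BAAB, BABA.
- In AABB and BBAA, positions 3 and 4 are both determined.
- In the other four, only position 4 is determined.
- Certain allocations per block = (2 × 2 + 4 × 1) / 6 = 1.333. As a share, 1.333 / 4 = 33.3%.
- By position the probability of certainty is 0, 0, 1/3 and 1.
- In 526 participants, 526 / 3 ≈ 175, if every block is complete.

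**3. Best guess.** Guessing the arm with more places left is right with probability 1/2, 2/3, 2/3 and 1 at positions 1 to 4. The mean is (0.5 + 0.667 + 0.667 + 1) / 4 = 70.8%, against 50% with no information.

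**4. Alternatives.** Fixed blocks of 6 and 8 come from the same enumeration. The varying lengths were simulated against an observer who knows the set of possible lengths and all past allocations in the centre. The lengths are illustrative.

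| Scheme | Known with certainty | Best guess correct |
|---|---|---|
| Fixed 4 (protocol) | 33.3% | 70.8% |
| Fixed 6 | 25.0% | 68.3% |
| Fixed 8 | 20.0% | 66.6% |
| Varying 4/6 | about 5.5% | about 69% |
| Varying 4/6/8 | about 2.3% | about 68% |

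**5. How sensitive the verdict is.** Expected events are 263 × 0.036 + 263 × 0.011 = 9.5 + 2.9 ≈ 12. Take 12 events, 263 per arm and a simple Wald interval, chosen here for illustration. With d = risk in 3HP-PUMCH minus risk in 9H, the upper limit is d + 1.96 × √[(p₁(1 − p₁) + p₂(1 − p₂)) / 263].
- 8 (9H) versus 4 (3HP-PUMCH): −1.52% + 2.55% = 1.03%. Below 1.4%, so non-inferior.
- 7 versus 5: −0.76% + 2.55% = 1.79%. Above 1.4%, so not shown.

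Newcombe limits are 1.24% and 2.06%, with the same two verdicts.

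**6. How much steering that would take from the planned rates.** At 3.6% and 1.1% the expected Wald upper limit is −2.5% + 2.58% ≈ 0.1%. Suppose each steered patient of risk r is exchanged between arms for an average patient of risk 3.6%, always moving the higher risk to 3HP-PUMCH. Each swap shifts the risk difference by 2(r − 0.036) / 263. The protocol gives no value for r.
- r = 10%: 0.049 points per swap, so about 27 swaps to reach 1.4%.
- r = 20%: 0.125 points per swap, so about 11 swaps.

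**The case against.** **The premises behind one third are not all stated.** Open label means that treatment is known after assignment. It does not show that any one recruiter followed a centre's whole sequence. The protocol is described as supporting information to a manuscript (section 5.4), and nothing shows that sites held the block length while enrolling. This stands, so one third is an upper bound for an informed recruiter. Incomplete last blocks lower it slightly.

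**A reader might infer that steering a few high-risk patients would overturn the result.** The documents do not support that in general. Steering moves risk, not events, so the effect of one event (1/263, or 0.38 points) does not measure it. From the planned rates it would take about 11 to 27 swaps in one direction, at the assumed risks. Fewer would suffice only if the result already lay near the margin.

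**Small fixed blocks have a purpose, and a central web system was used.** Both are true. Blocks of 4 keep the arms close to balanced within each centre. But varying lengths give up only a little of that balance, and the web system does not stop deduction from allocations already seen.

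**The remedy may come too late.** Section 3.3 and the consent statement in section 5.2 are in the past tense, while the data collection and analysis sections are largely in the future tense. Enrolment status cannot be settled from the text, so the fix must cover both cases.

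**Conclusion.** The point holds as an avoidable weakness of design. Under the stated scheme, up to one third of allocations (about 175 of 526) can be known in advance, and a best guess is right 71% of the time. Both figures assume that the recruiter knows or infers the block length and tracks the centre's earlier allocations.

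It would be tempting to read this as showing that the trial is biased. The documents do not show that: they establish opportunity, not its use. Nothing in section 3.3 is miscalculated, and the sample size is unaffected. The consequence is largest if the observed difference falls close to 1.4%, where moving one of about 12 events between arms can change the conclusion.

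**What to change.** **If allocations remain.** Set the central web system to randomly varying block lengths within centre (for example 4, 6 and 8) for all of them. Hold the lengths in a restricted randomisation document, and have section 3.3 say only that lengths vary and are withheld from recruiting staff. The cost is a configuration change, one protocol sentence and slightly looser balance in small centres. The gain is mainly the loss of certainty (33% to about 2%), which is what makes deliberate steering reliable. Guessing improves little, from 71% to about 68%.

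**If allocation is complete.** State whether recruiting staff knew the block length. Then compare baseline risk factors (such as steroid dose, immunosuppressant use, planned TNF inhibitor and underlying disease) between arms, separately for predictable positions (every fourth, and the third after two matching allocations) and unpredictable ones. A difference between arms confined to the predictable positions would point to selection. The cost is a short analysis of data already collected. With about 175 predictable allocations it can miss modest steering, so a clean result reassures but does not prove its absence.

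### The one listed outcome that counts adverse reactions depends on a causality judgement for which the protocol states no blinding, so uneven attribution in either direction could create or hide a safety difference

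*Protocol*

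**What the plan says.** The relevant statements, all from the protocol:

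- **Objectives, item 2:** "To compare the safety profile and treatment completion rates between the two regimens".
- **3.1 Study design:** "The study is a multi-center, open-label, non-inferiority, randomized controlled trial".
- **3.5 Secondary outcomes, item 1:** "Permanent discontinuation of TPT due to serious adverse events (SAEs) or ATB occurrence". This wording carries no relatedness condition.
- **3.5 Secondary outcomes, item 2:** "ADRs related to prophylactic drugs (assessed by WHO-UMC causality criteria"). No assessor is named and no blinding is stated.
- **3.5 Primary outcomes, diagnosis adjudication:** "All suspected ATB cases were reviewed by an external Endpoint Event Adjudication Committee", whose members are blinded to regimen. Section 4 gives the same remit: to "independently review and validate all primary outcome events (ATB), ensuring objectivity and consistency".
- **3.7 Secondary outcome analysis:** "The rates of adverse drug reactions (ADR), liver toxicity, and other outcomes will be compared using chi-square tests", with 95% confidence intervals.
- **3.7 Sample size, item 3:** the assumed benefit of the experimental arm is supported in part by adherence and protection, "as well as the expected reduction in toxicity with the modified regimen".
- **3.6 Follow-up procedures:** adverse events are recorded, and blood-count, liver and renal tests are done, at months 1, 2 and 3 in the 3HP-PUMCH arm and at months 1, 2, 3, 6 and 9 in the 9H arm.

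**The concern.** An outcome defined by relatedness has two parts: whether an event happened, and whether someone blamed the study drug for it. Randomisation makes the first comparable between arms. It does nothing for the second if the person judging knows the arm.

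The second part carries a lot of weight in this population. The Background section says that organ damage and other medication, which it regards as nearly unavoidable here, raise the risk of adverse reactions. The eligibility criteria admit patients on methotrexate, leflunomide, azathioprine, cyclophosphamide and similar drugs, and section 3.4 lets background therapy change during the trial. An abnormal liver test or blood count can therefore often be assigned to preventive treatment or to something else, and either assignment can be defended.

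The protocol protects its other judgement-based outcome, active TB, with an external blinded committee. It gives the adverse-reaction outcome no comparable protection and lists no all-cause counterpart. What is at stake is the safety half of objective 2: equal toxicity could look unequal, or a real difference could be attributed away.

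**Working it through.** **1. Sample size used.** Take control incidence 3.6%, experimental incidence 1.1%, margin 1.4%, one-sided alpha 0.025 and power 80% (section 3.7). With unpooled variance:

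n = (1.960 + 0.842)² × (0.036×0.964 + 0.011×0.989) / (0.014 + 0.025)² = 235.2, which rounds up to 236 per group.

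Dividing by 0.90 for attrition gives 263 per arm, or 526 in total. Both stated figures reproduce. They concern the primary outcome and serve here only to fix n = 263.

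**2. Which outcomes pass through the causality judgement?**

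| Item | Relatedness judgement needed? | Protected from knowledge of the arm? |
|---|---|---|
| Active TB | No | Yes, blinded committee |
| Secondary outcome 1 (stopping for SAE or TB) | Not in its wording | No, the decision to stop is open-label; also mixes safety with TB |
| Secondary outcome 2 (ADRs) | Yes | None stated |
| Liver toxicity (named only in 3.7) | Not defined | Not stated |

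No row is an all-cause adverse-event count.

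**3. Illustration with equal true toxicity.** The protocol gives no adverse-event rate and no attribution rate, so every input in this step is an assumption. Let r be the true all-cause rate in both arms, and a₁ and a₂ the shares attributed to preventive treatment. The recorded ADR rates are p₁ = r·a₁ and p₂ = r·a₂. The chance of a two-sided 5% result, by the normal approximation to the chi-square test, is

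Φ[(d − 1.96·s₀)/s₁] + Φ[(−d − 1.96·s₀)/s₁],

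where d = p₁ − p₂, s₀ = √(2p̄(1−p̄)/n), p̄ is the mean of p₁ and p₂, and s₁ = √(p₁(1−p₁)/n + p₂(1−p₂)/n).

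First row in full: r = 30%, a₁ = 70%, a₂ = 50%, so p₁ = 21%, p₂ = 15%, d = 0.06. With n = 263, s₀ = 0.0335 and s₁ = 0.0334, so (0.06 − 1.96×0.0335)/0.0334 = −0.17 and Φ(−0.17) = 0.43. The second term is negligible.

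| r (both arms) | Attribution | Recorded ADRs | False-positive rate, n = 263 | n = 236 |
|---|---|---|---|---|
| 30% | 70% v 50% | 21% v 15% | 43% | 40% |
| 30% | 60% v 50% | 18% v 15% | 15% | 14% |
| 20% | 70% v 50% | 14% v 10% | 29% | 27% |
| 20% | 60% v 50% | 12% v 10% | 11% | 11% |

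With equal attribution the rate is the nominal 5%. The arms are the same size, so swapping which arm has the higher attribution gives the same figures.

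**4. The reverse case.** Suppose true rates of 30% and 20%, with 40% attributed in the first arm and 60% in the second. Recorded ADRs are 0.30×0.40 = 12% and 0.20×0.60 = 12%. A 10-point true difference disappears.

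**5. What the data already collected allow.** The treatment-period visits are three in one arm (months 1, 2, 3) and five in the other (months 1, 2, 3, 6, 9). Counting participants who were ever abnormal over the whole treatment period would set three tests against five. Months 1, 2 and 3 are common to both, so any attribution-free comparison should use that window.

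**The case against.** **Other safety outcomes exist.** Secondary outcome 1 involves SAEs without a relatedness condition, and section 3.7 also compares liver toxicity. This stands to the extent that the ADR item cannot be called the only safety outcome. It does not remove the problem. Outcome 1 captures only events that end treatment and combines them with TB, while liver toxicity is not a listed outcome and has no definition that makes it independent of attribution.

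**The direction of bias is not established.** A reader might infer that the stated expectation of less toxicity would tilt attribution in favour of 3HP-PUMCH. The documents do not support going that far. The phrase names no comparator and sits in the sample-size rationale for TB. The Background raises a safety concern about 3HP in Chinese patients before introducing the modification, so the phrase may mean less toxic than standard 3HP, not than 9H. Knowing that a patient takes a second drug could also raise attribution in the experimental arm.

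**The assessor is not named.** It is therefore an inference that arm-aware staff make the judgement. That is fair, but the design is open-label and the only blinded body has a remit confined to TB.

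**Safety tables are commonly left to the SAP.** This is true of table layouts and cut-offs, and an SAP not shown here may include all-cause tables. The outcome definition and the committee's remit, however, are fixed in the protocol, and an SAP cannot blind a judgement already made at a site.

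**The magnitude is assumed.** This stands in full. The 43% needs a 20-point attribution gap; the 10-point cases give 11% to 15%.

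**Conclusion.** The point holds in a limited form. As defined, the listed adverse-reaction outcome can create or hide a between-arm difference through attribution alone, in either direction, and the protocol states no safeguard against this.

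The size cannot be determined from the document. With assumed all-cause rates of 20% to 30% and attribution gaps of 10 to 20 points, the false-positive rate at 263 per arm is about 11% to 43%. Those figures show what is possible; they do not predict what happened in this trial. They also do not show bias in favour of 3HP-PUMCH, for the reasons given above.

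The outcome is secondary and its analysis is headed as descriptive. The non-inferiority decision and the sample size are untouched. This is a worthwhile, inexpensive improvement to the evidence for objective 2, not a flaw in the trial's main conclusion.

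**What to change.** In sections 3.5 and 3.7, keep the WHO-UMC outcome and add two outcomes beside it, both counted regardless of judged cause:

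- (a) all-cause adverse events by grade;
- (b) liver and blood-count abnormalities defined by fixed laboratory thresholds, from the tests already scheduled.

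Define the liver toxicity named in 3.7 through the liver part of (b). Compare (a) and (b) between arms over the visits common to both treatment schedules (months 1 to 3). Report each arm's full treatment period separately, with its observation time.

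**Cost:** outcome wording and two extra tables. Section 3.6 already provides for the adverse-event records and the tests, so no visits, tests or participants are added. All-cause rates will be higher and noisier than ADR rates. All-cause reporting also stays unblinded, so the laboratory-defined events are the most robust part. Blinded causality review would go further but needs extra staff, and the improvement does not depend on it.
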